*Functional activation: cue reactivity:* One of the most prominent models of addiction is incentive sensitization (Robinson and Berridge, 2001), where the brain mesocorticolimbic reward system is sensitized, and drug cues acquire motivational salience and become conditioned reinforces themselves. In the case of smokers, smoking-related environmental stimuli can elicit smoking urges and cravings, which in turn is associated with compulsive smoking and relapse. Most neuroimaging studies examining neural reactivity to smoking-related (compared to neutral) cues have shown that smokers exhibit increased activation in regions involved in reward, craving, emotions, and memory, as well as regions associated with visuospatial attention (Due, 2002), suggesting increased attention to stimuli of heightened attentional salience. One study found that hyper-activation in some of these regions and decreased connectivity with cognitive control networks predicted “slips” in abstinence (Janes et al, 2010), and behavioural and non-nicotinic pharmacological smoking interventions can normalize these brain responses relative to non-smoking controls (Culbertson et al, 2011; Franklin et al, 2011; Westbrook et al, 2013). However, only a small number of studies have examined the effect of varenicline treatment on smoking cue reactivity. Although these studies suggest that varenicline modulates relevant networks, none of these studies used a full 12-week treatment protocol one study only required 3 days of abstinence prior to the second scan (Loughead et al, 2013), and another study required subjects to be non-abstinent even after 3 weeks of medication (Franklin et al, 2011). Our study will address this gap in the literature by conducting fMRI scans at baseline and after 12-weeks of varenicline treatment in both the active and sham treated tDCS groups. The sham tDCS group will allow us to examine the effects 12-weeks of varenicline treatment on cue reactivity in both quitters and non-quitters. Furthermore, we can compare the treatment effects of active versus sham tDCS within-subjects by comparing the pre- and post-treatment scans. Active tDCS should reduce cue-reactivity by increasing plasticity of the left DLPFC.

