**Hypotheses**:

1. The combination of varenicline treatment plus tDCS to the left DLPFC will improve smoking cessation outcomes and relapse rates in treatment seeking smokers.
2. Active tDCS will reduce fMRI BOLD response to smoking cues compared to baseline within-subjects and compared to sham tDCS between subjects. Those who quit smoking in the last 4 weeks of treatment will show a “normalization” of brain reactivity to smoking cues and reward anticipation relative to those who were unable to remain abstinent over the short term due to tDCS extinguishing the salient properties of smoking-related cues and reward anticipation.
3. Compared to baseline, varenicline treatment will reduce within subject attentional bias, as measured by parameters of visual scanning behavior (VSB), to smoking and negative emotional cues.
4. Active tDCS will reduce attentional bias to smoking and negative emotional cues compared to sham tDCS. Those who quit smoking in the last 4 weeks of treatment will show “normalized” attentional bias patterns to smoking cues and reward anticipation relative to those who were unable to remain abstinent over the short term. Subjective measures of cravings will be correlated with within-subject changes in attentional bias to smoking cues and reward anticipation.
5. Individuals with larger changes in attentional bias to smoking-related cues and/or negative emotional cues, and lower measures of attentional bias to high-arousal/high-risk cues will have higher rates of abstinence (less relapse). Attentional bias will be measured by parameters of visual scanning behaviour and through the analysis of visual scanning patterns (sequences of fixations).
6. The probability of remaining abstinent over the long term will be inversely correlated with VSB measures of novelty seeking behavior.
7. Active tDCS will reduce impulsivity compared to sham tDCS as measured by higher delayed discounting scores.

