**METHODS**

**Design**

This will be a double-blind sham-controlled two-arm randomized clinical trial. Fifty participants will be randomized (1:1) to each arm. Arm 1 will be active tDCS plus varenicline (n=25) and Arm 2 will be sham tDCS plus varenicline (n=25). Treatment duration will be 12 weeks. Subjects will be required to attend an in person assessment visit. They will then be randomized to a condition. Neuroimaging scans (fMRI) and eye-tracking tests will be conducted in all participants at baseline. Participants will undergo two scans at baseline on different days within the same week: one in a satiated state and one in a non-satiated state. The same tasks will be performed at each scan. s. Following the baseline fMRI scans and eye-tracking tests, subjects will start taking the varenicline simultaneous with starting the tDCS regimen whereby they will come to the clinic every day (Monday to Friday) for the first 2 weeks to undergo the stimulation (active: 20 minutes at 2mA, sham: 30 seconds at 2mA and then nothing). Their target quit date will be at the end of this 2 week period. They will return to the clinic every two weeks for the next 10 weeks for a booster tDCS session and to complete questionnaires. Eye tracking tests will be conducted at the end of the fourth and eighth weeks. At the end of the 12-week treatment period they will undergo a third fMRI scan and eye-tracking tests. For the next 14 weeks they will be contacted weekly by e-mail or text message to report on their smoking status as measured by the 7 day point prevalence abstinence question. “Have you had a cigarette, even a puff, in the last 7 days?” At the 6-month time point subjects will be asked to return to the clinic for a brief visit to confirm smoking abstinence using expired CO and urinary cotinine and to complete questionnaires.

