**Participants**

Study participants will be 50 treatment seeking daily dependent smokers willing to make a quit attempt in the next 30 days. They will be recruited from our Nicotine Dependence Clinic and from the Greater Toronto Area through paid advertising in local newspapers and through the CAMH Registry and the CAMH website. Participants will have no concurrent Axis I psychiatric disorder (or history of substance use disorder), based on SCID, and be free of psychoactive drugs and medications, based on self-report and urinalysis. To ensure against subtle neurological deficits associated with sub-clinical alcohol misuse, men will be required to drink no more than 12 standard drinks per week and women will be required to drink no more than 9 drinks per week. These values conform to safe drinking limits for non-problem drinking (Sobell and Sobell, 1992). According to standard protocols for tDCS clinical trials, participants will also be excluded if they: a) have had recent clinically significant head trauma; b) have a history of seizures and/or epilepsy; c) are pregnant or planning to become pregnant; d) have pacemakers or implanted electrical devices such as cochlear implants; e) have metal embedded in the skull; or f) have skin lesions, open wounds, bruising, or similar injuries at either of the stimulation sites.

*Eligibility Criteria*

- Male or female
- Ages 19-65
- Daily smoker > 8 CPD
- Seeking treatment to quit smoking
- No current/recent DSM-IV Axis I diagnosis (apart from nicotine dependence)
- No current use of psychoactive drugs or medications
- No current use of Nicotine Replacement Therapy, e-cigarettes, or other medications for smoking cessation
- No history of seizures/epilepsy
- No metal embedded in the skull and/or implanted electrical devices
- No head injury (no concussion – diagnosed by a physician; OR no blow to the head with loss of consciousness for more than 1 hour)
- No known contraindications to fMRI
- No known contraindications to Varenicline
- Able to attend daily appointments for tDCS for the first 2 weeks and then once every 2 weeks for the next 10 weeks.
- Willing to undergo three fMRI scans – two at baseline and another at the end of treatment.

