**Sample Size and Power Calculation**

If we assume a 40% abstinence rate at end of treatment in the varencline plus sham tDCS group, the abstinence rate in the active tDCS group would need to be double that or 80% in order to see a statistically significant difference with n=25 per arm, p <0.05, and 80% power. As such we do not expect to see a statistically significant difference between the two treatment arms at 25 subjects per arm.

For the treatment part of the study, the main purpose of the study is to establish an Effect Size for tDCS as an adjunct to standard varenicline treatment. This is independent of the number of subjects but allows us to estimate the N that would be required to achieve statistical significance depending on the effect size we observe. The effect size measure we will use will be the partial η2 generated by SPSS and is described in greater detail below.

For the MRI portion of the study, 15 to 25 subjects per group is standard in the neuroimaging field and is more than sufficient to detect significant within- and between-group differences in brain activity.

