**Data Analysis**

Continuous data (cravings, mood, cigarettes smoked/day, CO) will be assessed with 2 Gender x 2 (Laterality) x 10 (session) Analyses of Variance (ANOVA). Parallel ANOVAs will assess self-report measures during post-treatment follow-up. Categorical data (e.g., # abstinent participants/session) will be assessed with chi-square, and Kaplan-Meyer survival analysis for repeated measures. Planned comparisons will be performed for the critical experimental conditions (active tDCS) vs. sham.

The critical metric will be Effect Size (partial η2 generated by SPSS), rather than p level. This will reveal the degree of efficacy for the primary outcome variable, Consecutive Days Abstinent (small = .01, medium = .06, large = .14), and allow us to estimate N required to achieve statistical significance for this effect (80% power, α = .05, two-tailed). Pearson correlations will explore the possible relationship between effects of tDCS (session 10 scores, controlling for session 1) and trait factors (e.g., FTND, age, gender, depression).Analysis of MRI data

For the neuroimaging data, brain imaging measures will be compared between groups and across time points, using analysis of variance. MRI measures will also be related to subjective responses (i.e., baseline scores and changes in craving, mood, and withdrawal) using linear regression.

fMRI data will be analyzed by fitting a general linear model (GLM) to the data time-series at every voxel across the brain (and/or within ROIs) and assessing effects using F/t-tests and % signal change calculations. Quantitative T1 maps and DTI analysis will be analyzed at the whole brain level and using ROIs.

After back-sorting by treatment outcome (achieved/maintained abstinence), we expect baseline measures to predict relapse, and active tDCS treatment to result in more efficient functional activation, . than sham tDCS at the second MRI scan.

Analysis of Eye-Tracking Data

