For the eye-tracking data, gaze position data are processed by VAST into sequences of fixations and saccades and summary statistics of visual scanning parameters are computed. The VAST parameters include: the number of fixations, the average fixation duration, the average saccadic amplitude and the number of transitions for each image type. These parameters are sensitive measures of attentional bias for different visual cues. The outcome measures of this paradigm will be analyzed using a mixed-model analysis of variance (ANOVA). The within-groups factors are the image types (smoking, neutral, high valence) and session (sessions 1, 2, 3,4 and 5) and the between-groups factor is group (active tDCS and sham tDCS). Pearson’s product–moment correlations will be conducted between parameters of attentional bias and subjective craving scores. Through analysis, we will investigate and compare the treatment effects of varenicline and active tDCS on attentional bias in different sessions. We will also examine the relationship between changes in attentional bias and craving.

By means of a mixed design repeated-measures ANOVA, the VAST parameters will be compared within-subjects at 5 sessions to investigate the effects of varenicline treatment. The parameters will also be compared between the two groups of subjects to examine the treatment effects of active tDCS. We will also compare the VSB parameters of those who quit smoking in the last 4 weeks of treatment and those who were unable to remain abstinent to find out the possible indicators of treatment outcome. Pearson correlation method will be used to explore the relationships between: a) subjective craving and VSB parameters, b) sensation seeking behavior as measured by the sensation seeking scale measures and VSB parameters. Also we will use recurrent neural networks (Chung et al, 2018) to analyze differences between fixation sequences of patients that were treated with tDCS and patients that were not, and between patients that quit smoking and those that were not. Using Cox regression of survival analysis, we will also investigate the correlation between the length of abstinence (time to relapse) and VSB parameters associated with smoking cues, negative emotional cues and high-arousal/high-risk cues.

All data analysis will be conducted using SPSS, SPM or R as appropriate.

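### Hypothesis 2 credits tDCS with a non-randomised quitter versus non-quitter difference that need not come from tDCS, and hypotheses 2 and 4 call such a difference normalization in a trial that enrols only smokers

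*Protocol*

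**What the plan says.** Hypotheses 2 and 4 (Protocol, Hypotheses) each open with a randomised prediction: active tDCS will lower the response to smoking cues, or attentional bias, compared with sham. Each then adds a prediction about quitters.

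- Hypothesis 2 says those who quit in the last 4 weeks of treatment will show normalization of their brain response, both to cues and when a reward is expected, "relative to those who were unable to remain abstinent over the short term due to tDCS extinguishing the salient properties of smoking-related cues".
- Hypothesis 4 says those who quit "will show “normalized” attentional bias patterns to smoking cues and reward anticipation relative to those who were unable to remain abstinent". This sentence gives no cause.

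The Background uses the same word for earlier interventions, which "can normalize these brain responses relative to non-smoking controls". The trial itself has no such controls. Under Participants, "Study participants will be 50 treatment seeking daily dependent smokers", and Design allocates them 1:1 to active or sham tDCS, 25 per arm, all on varenicline.

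Data Analysis carries the quitter theme forward. For MRI: "After back-sorting by treatment outcome (achieved/maintained abstinence), we expect baseline measures to predict relapse"; the sentence goes on to expect active tDCS to differ from sham. For eye tracking: "We will also compare the VSB parameters of those who quit smoking in the last 4 weeks of treatment and those who were unable", the latter being participants who did not stay abstinent. That comparison does not mention arm.

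**The concern.** Two inferences in the hypotheses go further than the comparisons attached to them.

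The first is causal. Quit status is not randomised, and nothing in the quitter sentence of hypothesis 2 confines it to the active arm. The Protocol itself supplies other routes to the same result. The Background says that varenicline modulates the relevant networks and that non-tDCS interventions can change these responses. Hypothesis 3 expects varenicline treatment to reduce attentional bias. The Neuroimaging section scans baseline in abstinent and satiated states, so recent smoking is treated as relevant, and quitters and non-quitters will differ on it at the third scan.

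The second is the word *normalization*, which needs a normal reference.

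At stake is the secondary objective, which concerns adaptations resulting from tDCS. If hypothesis 2 is read as written, a quitter effect with no tDCS effect behind it would appear to confirm it.

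**Working it through.** **Inputs**

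- 25 per arm, 1:1 (Design).
- Sham abstinence 40% (Sample Size and Power Calculation: "If we assume a 40% abstinence rate at end of treatment in the varencline plus sham tDCS group").
- Active abstinence is not predicted. The same section gives 80% as the rate needed for significance and does not expect a significant difference. I take 40% to 80% as the range; the 60% midpoint is my assumption.

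**1. The plan's own figure.** For 40% versus 80%, two-sided 0.05, 80% power:

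n per arm = [1.96√(2 × 0.6 × 0.4) + 0.84√(0.4 × 0.6 + 0.8 × 0.2)]² / 0.4² = 22.3, so 23. With continuity correction it is 28. At 25 per arm, power is 84.5% by the normal approximation and 78.8% by Fisher's exact test. The stated 80% reproduces.

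**2. Who the quitters are.** Sham quitters = 0.40 × 25 = 10. Sham share of quitters = p_sham / (p_sham + p_active).

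| Active abstinence | Active quitters | All quitters | Sham share of quitters | Active share of quitters | Active share of non-quitters |
|---|---|---|---|---|---|
| 40% | 10 | 20 | 10/20 = 50% | 50% | 15/30 = 50% |
| 60% | 15 | 25 | 10/25 = 40% | 60% | 10/25 = 40% |
| 80% | 20 | 30 | 10/30 = 33% | 67% | 5/20 = 25% |

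The share depends only on the ratio of the two rates. It stays between 50% and 33% whenever the active rate is one to two times the sham rate, whatever the sham rate is.

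**3. What the pooled contrast measures.** Suppose tDCS shifts a measure by δ in everyone who receives it, and quitters differ from non-quitters by γ for other reasons (abstinence itself, response to varenicline, baseline dependence). Then

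pooled contrast = γ + δ × (active share of quitters − active share of non-quitters).

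From the table the multiplier of δ is 0, 0.20 or 0.42. If δ = 0, the contrast still equals γ and can be clearly positive. If the abstinence rates are equal, the contrast contains none of δ.

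**4. Restricting to the active arm does not rescue the clause.** There, quitters and non-quitters have all been assigned tDCS, so a difference between them cannot be credited to tDCS without the sham arm as comparison.

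**5. What arm by quit status could show.** With complete scans and a common SD, the SE of the interaction in SD units is √(sum of 1/cell size), and the detectable effect is (1.96 + 0.84) × SE.

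- 80% versus 40%: cells 20, 5, 10, 15; SE = √0.417 = 0.65; detectable effect about 1.8 SD.
- 60% versus 40%: cells 15, 10, 10, 15; SE = √0.333 = 0.58; detectable effect about 1.6 SD.

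**6. Normalization.** In the Background the word is tied to non-smoking controls. In hypotheses 2 and 4 the stated comparator is participants who did not stay abstinent, and Participants and Design provide no other. The direction is also not uniform. Lower reactivity to smoking cues would fit the rationale, but the Background describes blunted responses to non-drug reward in addicted people and links lower ventral striatal activity to relapse. On that account, normal striatal reward anticipation would be higher. Hypothesis 2 gives no direction for quitters, so a shift either way could be called normalization.

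**The case against.** The strongest defence is that the plan already contains the right test. Both hypotheses open with active versus sham. Data Analysis compares imaging between groups and over time, and specifies a mixed ANOVA with group and session for eye tracking. The MRI sentence that sorts by outcome still expects active to differ from sham, and the Background says the sham arm will show varenicline's effects in quitters and non-quitters alike. All of that stands. It means the secondary objective keeps a randomised test. It does not repair the separate sentence that attaches a tDCS cause to the quitter contrast.

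It can also be said that normalization is placed in quotation marks in both hypotheses with its comparator named, and that the Background uses the term for cited work, not as a trial endpoint. This is fair, and it makes the matter one of wording. The wording still promises something the comparator cannot deliver.

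A reader might infer that neither hypothesis can be tested. The documents do not support that. The difference between quitters and non-quitters can be tested and is planned for eye tracking. Sham quitters do not make the attribution untestable; they are the group that could count against it. A reader might also extend the causal complaint to hypothesis 4, but its quitter sentence credits nothing to tDCS.

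Finally, covariates for a secondary comparison are often left to the analysis plan. That is so, and the absence of arm from the model is not itself the fault. The fault is the causal clause in the hypothesis.

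**Conclusion.** The point holds in a limited form. The pooled quitter versus non-quitter contrast cannot support the causal clause in hypothesis 2, and the trial cannot show a return to normal under hypothesis 2 or 4. It can show a difference from non-quitters or a change from baseline.

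The size is conditional. With sham abstinence at 40% and active abstinence between 40% and 80%, sham participants would be expected to be 50% to 33% of quitters. That share describes who is in the group; it is not an estimate of bias. The logical objection does not depend on it, because quit status is a post-randomisation outcome under any rates.

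The primary outcome and the randomised active versus sham predictions are untouched. The correction is worth making because it changes what may be concluded about mechanism, and it is cheap.

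**What to change.** - In hypothesis 2, delete the clause crediting tDCS from the quitter sentence.
- In hypotheses 2 and 4, replace normalization with a difference between quitters and non-quitters in change from baseline, with the direction stated per measure: a reduction for smoking-cue reactivity and attentional bias, and for reward anticipation a direction consistent with the blunted-response rationale in the Background. A blanket prediction of larger reductions would contradict that rationale.
- State that the tDCS mechanism is judged on the randomised arm by time contrast already planned for imaging and eye tracking.
- Include arm in the quitter versus non-quitter comparisons and report them as associations. Label any arm by quit-status interaction exploratory, since expected cells may be as small as 5 and only effects of about 1.6 to 1.8 SD are detectable.

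This needs no extra participants, scans or visits: two hypotheses are reworded and one term is added to planned comparisons. The price is a more modest mechanistic claim.

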**METHODS**

**Design**

This will be a double-blind sham-controlled two-arm randomized clinical trial. Fifty participants will be randomized (1:1) to each arm. Arm 1 will be active tDCS plus varenicline (n=25) and Arm 2 will be sham tDCS plus varenicline (n=25). Treatment duration will be 12 weeks. Subjects will be required to attend an in person assessment visit. They will then be randomized to a condition. Neuroimaging scans (fMRI) and eye-tracking tests will be conducted in all participants at baseline. Participants will undergo two scans at baseline on different days within the same week: one in a satiated state and one in a non-satiated state. The same tasks will be performed at each scan. s. Following the baseline fMRI scans and eye-tracking tests, subjects will start taking the varenicline simultaneous with starting the tDCS regimen whereby they will come to the clinic every day (Monday to Friday) for the first 2 weeks to undergo the stimulation (active: 20 minutes at 2mA, sham: 30 seconds at 2mA and then nothing). Their target quit date will be at the end of this 2 week period. They will return to the clinic every two weeks for the next 10 weeks for a booster tDCS session and to complete questionnaires. Eye tracking tests will be conducted at the end of the fourth and eighth weeks. At the end of the 12-week treatment period they will undergo a third fMRI scan and eye-tracking tests. For the next 14 weeks they will be contacted weekly by e-mail or text message to report on their smoking status as measured by the 7 day point prevalence abstinence question. “Have you had a cigarette, even a puff, in the last 7 days?” At the 6-month time point subjects will be asked to return to the clinic for a brief visit to confirm smoking abstinence using expired CO and urinary cotinine and to complete questionnaires.

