**Procedures**

Following the initial assessment appointment to obtain consent and confirm eligibility, the first tDCS treatment session will be booked. A breathalyser will screen for alcohol and expired CO at each tDCS session. The tDCS stimulation will take place in a quiet room, free of distractions. Stimulation will continue uninterrupted for 20 minutes with the experimenter in the room. While being stimulated, subjects will be required to read self-help materials related to smoking cessation, relapse prevention, and mood management. The readings for each day of stimulation will be standardized for all subjects.

To increase the opportunity to detect an acute beneficial effect of tDCS, participants will be asked to refrain from smoking for 2 hours prior to the start of each treatment session. Relative CO readings from the first day (ad lib smoking) compared to subsequent days will provide a coarse means of verifying compliance with the 2-hour pre-session smoke-free requirement.

Participants will be randomly assigned (1:1) to one of 2 treatment arms (double-blind). Participants will be matched as closely as possible on age, gender and cigarettes per day.

There will be 10 consecutive daily sessions of tDCS with the anode over the left DLPFC and cathode over the right DLPFC (active or sham) (Monday-Friday for 2 weeks; 2 mA x 20 min). Participants assigned to sham will have electrodes placed identically to active but receive only 30 seconds active stimulation. Participants will also be videotaped during each tDCS session to ensure consistency of tDCS application between research personnel and for documenting participant reactions during the session. This will also be used to document any side effects/complications participants may experience during the session. Each video tape session, as well as all data collected in the trial, will be stored on a secure server and will be retained for 10 years after the participant completes the study, as suggested by CAMH’s policy on Storage of Records. After each tDCS session, the video footage will be transferred from the camera to the secure server.

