**Neuroimaging**

The fMRI neuroimaging component to this study will attempt to answer several research questions and address some of the gaps in the tDCS literature. Specifically, how does tDCS and/or varenicline alter functional connectivity between PFC and amygdala or insula? Does the magnitude of change predict successful cessation and long-term abstinence? Does active tDCS change the BOLD response to smoking cues and/or emotional cues? What is directionality of this effect?

Prior to MRI scans, participants will be required to complete a training session at least 24 hours prior to their first scan using the mock MRI scanner, a device which stimulates the scanner conditions including the screen-response apparatus. MRI tasks will be explained to participants outside the scanner and they will then be able to complete mock versions of the cue-reactivity and reward anticipation tasks. Participants who cannot appropriately complete the tasks or who demonstrate excessive motion or discomfort in the scanner due to the confined environment will be excluded from participation in the study.

Magnetic resonance imaging (MRI) will take place at the CAMH Research Imaging Centre (GE Discovery MR750 3T, General Electric Medical Systems, Milwaukee, WI) on 3 occasions: 1) at baseline following 12 hours of smoking abstinence (abstinence scan) 2) at baseline within 1 hour of smoking a cigarette (satiated scan) and 3) at end of the 12 week varenicline treatment. Baseline scans will occur within 1 week of each other and the order of satiated and abstinent scans will be counterbalanced to control for possible order effects. During each session, we will measure: 1) functional activation (blood-oxygen-level-dependent (BOLD) response) while subjects perform cue reactivity and reward anticipation task; resting state functional connectivity (rsFC) 3) quantitative T1 mapping (qMRI) and/or 4) Diffusion Tensor Imaging (DTI).

*Measures at rest*

The following measures (rsFC, DTI, qT1) will be collected with the subject at rest, i.e., no task performance will be required. qT1 images will be acquired across the whole brain. Diffusion Tensor Imaging (DTI)

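### Randomisation is placed before the baseline scans and eye-tracking, so the whole-study mock-scanner exclusion can fall, and baseline withdrawals do fall, after allocation but before treatment

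*Protocol*

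**What the plan says.** The Design section of the protocol sets out the sequence. It begins with "Subjects will be required to attend an in person assessment visit" and continues "They will then be randomized to a condition". The next step is "Neuroimaging scans (fMRI) and eye-tracking tests will be conducted in all participants at baseline", with two scans on different days in the same week, and treatment comes last: "Following the baseline fMRI scans and eye-tracking tests, subjects will start taking the varenicline simultaneous with starting the tDCS regimen".

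The Procedures section describes what the assessment visit is for: "Following the initial assessment appointment to obtain consent and confirm eligibility, the first tDCS treatment session will be booked". It does not mention the mock scanner.

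The Neuroimaging section adds a further step: "participants will be required to complete a training session at least 24 hours prior to their first scan using the mock MRI scanner". People who cannot do the tasks, or "who demonstrate excessive motion or discomfort in the scanner due to the confined environment will be excluded from participation in the study", leave the trial altogether and not just its imaging part. The eligibility list under Participants covers fMRI contraindications and willingness to have three scans, but not performance or tolerance in the mock scanner.

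On the allocation itself, Procedures specifies random 1:1 assignment, double-blind, and then adds: "Participants will be matched as closely as possible on age, gender and cigarettes per day". No mechanism is named.

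**The concern.** A check that removes people from a trial belongs before allocation. If it comes after, some of the 25 per arm are used up on people who never start treatment. The arms can become unequal by chance, and the team must decide whether those people count in the abstinence analysis. The same applies to people who withdraw over the two baseline scan days.

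The arms here are small: one participant is 1/25 = 4% of an arm. The section on sample size says that the main product of the treatment part is an effect-size estimate for sizing a later trial, so the number and balance of people who start treatment feed directly into what the trial is meant to deliver.

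The matching sentence raises a smaller question. Participants enter one at a time, so balance on age, gender and cigarettes per day requires some stated procedure, and the reader cannot tell which one is meant.

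**Working it through.** **Order of steps, from the text**

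| Step | Where stated | Position relative to randomisation |
|---|---|---|
| Assessment visit: consent, eligibility | Design; Procedures | Before |
| Randomisation | Design | – |
| Mock-scanner session, with whole-study exclusion | Neuroimaging | Not fixed; only at least 24 h before the first scan |
| Two baseline fMRI scans, baseline eye-tracking | Design | After |
| Start of varenicline and tDCS | Design | After |

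Two things follow. The mock session may fall on either side of allocation. The baseline scans and eye-tracking fall after allocation, so anyone who withdraws during them is a loss after randomisation, however the mock session is scheduled.

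**Inputs for the size**

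- From Sample Size and Power Calculation: sham rate 40%, active rate 80%, 25 per arm, alpha 0.05, power 80%.
- Two-sided testing: stated under Data Analysis for the estimate of a future N, and assumed here too.
- Share lost between allocation and treatment: not in the protocol. Assumed 12–20%, equal in both arms.

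**Reproducing the protocol's figure**

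Normal approximation with pooled variance under the null, p̄ = (0.40 + 0.80)/2 = 0.60:

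n = [1.960·√(2·0.60·0.40) + 0.842·√(0.40·0.60 + 0.80·0.20)]² / 0.40² = (1.358 + 0.532)² / 0.16 = 22.3, so 23 per arm.

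Power at 25 per arm: z = (0.40·√25 − 1.358)/0.632 = 1.015, giving 84.5%. The exact power of the two-sided Fisher test is 78.8%. The protocol's statement of 40% against 80% with 25 per arm is therefore reproduced.

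**Effect of losing 12–20% before treatment**

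Remaining per arm: 25 × 0.88 = 22; 25 × 0.80 = 20.

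If those lost are dropped from the analysis:

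| Per arm | z for 40% vs 80% | Power, normal approx. | Power, Fisher | Active rate detectable vs 40%, 80% power, normal approx. |
|---|---|---|---|---|
| 25 | 1.015 | 84.5% | 78.8% | 78.1% |
| 22 | (0.40·√22 − 1.358)/0.632 = 0.819 | 79.4% | 69.1% | 80.3% |
| 20 | (0.40·√20 − 1.358)/0.632 = 0.681 | 75.2% | 65.0% | 82.0% |

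If instead everyone randomised is kept and those lost count as smokers, both rates shrink by the factor (1 − d) with 25 per arm:

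- d = 12%: 35.2% vs 70.4%; z = (0.352·5 − 1.384)/0.661 = 0.570; power 71.6%.
- d = 20%: 32% vs 64%; z = (0.32·5 − 1.385)/0.669 = 0.322; power 62.6%.

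Under the second treatment the expected difference itself falls from 40 points to 35.2 or 32 points. So the way these people are counted changes the effect estimate as well as the power. Randomising later removes the question for losses at the mock session and at baseline.

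**The case against.** **The protocol never says that the mock session follows randomisation.** This is correct. A site could hold it at the assessment visit, or between that visit and allocation, and the imaging-related eligibility criteria make a screening reading possible. A reader might infer a stated rule of allocating first and excluding afterwards; the text does not support that. What stands is that nothing requires the earlier timing, and that the baseline scans and eye-tracking are placed after allocation.

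**Such losses need not bias the comparison.** This also stands. They would come before any treatment and would turn on motion, discomfort or task performance. In a trial described as double-blind, these have no evident link to an allocation nobody has seen. A reader might conclude that the randomised comparison is broken, or that the baseline measures are contaminated by knowledge of the arm. Neither follows if allocation is concealed.

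**Power is not this trial's criterion.** The section on sample size says outright that no significant difference is expected at 25 per arm. The shift of roughly 2 to 4 points in the detectable rate is therefore secondary and rests on an assumed loss. The effect on the estimate and on the numbers starting treatment remains.

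**Matching may be loose wording.** Stratification and minimisation both balance factors in sequential enrolment by algorithm. A reader might infer that staff steer assignments by hand, or that the 1:1 allocation can be overridden. The protocol says neither. Details of the method may also be in a document not shown. What remains is that the sentence, standing beside random assignment, does not say what is done.

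**The chi-square test does not adjust for the balancing factors.** Adjusting a binary outcome for three factors with 25 per arm has costs of its own. It is a trade-off, and the absence of adjustment is not an error.

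**Conclusion.** The point holds as a defect in the order of steps. Allocation comes before the baseline scans and eye-tracking, and a whole-study exclusion is left free to fall after it. A site that follows the text can lose allocated participants before any of them is treated.

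The size is modest and conditional. With an assumed 12–20% loss, equal in both arms, the arms fall from 25 to 22–20, and the active rate detectable against 40% rises from about 78% to about 80–82%. With no loss there is no effect. Provided allocation is concealed, the consequences are fewer participants, possible chance imbalance and an unclear analysis population. The change is worth making because it is cheap and protects the effect-size estimate that the trial exists to provide.

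The matching sentence is a secondary point that needs clarifying and is not evidence of a compromised randomisation.

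**What to change.** Amend the Design section so that randomisation follows the mock-scanner session, both baseline scans and baseline eye-tracking, for example at the first tDCS visit. People who fail or withdraw before that point are then replaced before allocation. Add the mock-scanner requirement to the eligibility criteria and give its timing in the Neuroimaging section, so that the three sections agree.

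In Procedures, replace the matching sentence with the concealed balancing method actually used, such as stratified randomisation or minimisation with a random element.

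The cost is a short protocol amendment. Allocation moves by about a week, the target stays at 50 randomised, and no participant undergoes an added procedure. The downside is that a few more people are screened and scanned before randomisation. With an assumed 12–20% loss, about 50/0.88 = 57 to 50/0.80 = 63 people would have to enter this stage to leave 50 for allocation.
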